**Study endpoints**				
Comprehension of preventive service most likely and least likely to improve QALE^a^ Readiness to change (transtheoretical model) [40] Lifestyle^b^	Self-reported preventive (and chronic disease management) service utilization Lifestyle^b^	-	-	-
**Future directions**				
Interest in using individualized preventive care recommendations again in the future (Likert scale)			Suggestions for improvement	Would you like to keep using the tool? Are there obstacles?
**Other**				
Demographics Self-rated health			How well did the intervention fit with your clinical workflow? How can we improve workflow?	Patients for whom the tool was particularly helpful (not helpful) What other information would be helpful?

^a^ Left- and right-hand bars in Fig. 2

^b^ Tobacco use, alcohol (AUDIT-C) [31, 32], healthy diet (Starting the Conversation) [27, 28], physical activity (IPAQ-SF) [29, 30]

### Adverse events (harms)

As a minimal risk study, safety events are unlikely. However, because individualized recommendations may upset patients, we will measure anxiety/depression, defined as a new mental health diagnosis, score on the Generalized Anxiety Disorder[GAD]-7 questionnaire≥8 or Patient Health Questionnaire[PHQ]-8≥10 (asked in patient surveys) [41, 42]. Additionally, we also collect data on harms of preventive services that patients may choose to undergo (or not) due to the intervention, but it is very unlikely these would be study-related (full study protocol).

### Randomization

Provider randomization will be stratified by site (1:1 allocation ratio) in permuted block sizes of 2, 4, and 6. The study biostatistician will conceal the block sizes and generate the sequence with computer-generated random numbers. Study staff who enroll providers will not have access to the sequence; instead, they will communicate enrollment to designated study coordinators.

### Blinding

Because the nature of PDP requires frequent interaction with providers (e.g., intervention feedback), cluster randomization will be unblinded. However, the Principal and Co-Investigators, except the study biostatistician and safety assessor, will be blinded to stratification of outcomes and safety events by arm. The DSMB may request unblinding of specific participants.

### Collection of study endpoints

The primary outcome, change in patient QALE between the baseline encounter and 6 months later, and most secondary outcomes will be estimated through our mathematical model. Inputs will be obtained from an EHR data feed for each patient, from the baseline encounter through study completion. Select lifestyle endpoints with limited-no availability in the EHR (healthy diet, physical activity), wide variance in documentation quality (alcohol misuse) or that may have been changed since the last update in the EHR (tobacco) may be self-reported using validated scales in patient surveys [27–32]. The full study protocol specifies an objective algorithm in case EHR and self-reported data conflict.

### Statistical analysis

The biostatistician will conduct analyses based on an equivalence design, with a modified intention-to-treat (ITT) patient population. Each patient who completed the baseline primary care encounter (excluding no shows, cancellations, etc.) and his/her provider will be treated in the group according to initial randomization. Linear mixed-effect models with random intercepts at the patient and provider levels will be used. Such models assume data missing at random. Sensitivity analyses may consider full ITT and per protocol populations, as well as multiple imputation for missing data. Full ITT is not expected to yield significant results because approx. 1/3 of primary care patients do not show up or cancel scheduled encounters [20]. Subgroup analyses will be by race. There are no planned interim analyses.

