**Methods:**

The Personalized Disease Prevention (PDP) cluster-randomized clinical trial will evaluate whether patients and their providers benefit from an evidence-based decision tool to prioritize preventive services based on their potential to improve quality-adjusted life expectancy. The decision tool will be individualized for patient risk factors and available in the electronic health record. This Phase III trial seeks to enroll 60 primary care providers (clusters) and 600 patients aged 40–75 years. Half of providers will be assigned to an intervention to utilize the decision tool with approximately 10 patients each, and half will be assigned to usual care. Mixed-methods follow-up will include collection of preventive care utilization from electronic health records, patient and physician surveys, and qualitative interviews. We hypothesize that quality-adjusted life expectancy will increase by more in patients who receive the intervention, as compared with controls.

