### Endpoints

Table 3 shows primary, secondary, and select tertiary study endpoints. The primary objective is to measure whether use of the tool improves patient quality-adjusted life expectancy (QALE), at a 6-month timeframe. We chose this outcome as an aggregate measure of utilization, alleviating the need to separately consider each service and to allow for the differential impact of each service on patient health (e.g., tobacco cessation vs. tetanus shot). For context, a 3-month increase in QALE is roughly equivalent to any of the following: lowering systolic blood pressure (BP) 5 mmHg, losing 5 lbs., low-dose statins, or both colorectal and breast cancer screenings. Actual magnitudes depend on each patient’s evidence-based risk factors, which vary substantially across patients.

**Table 3 Tab3:** Study endpoints

Objectives	Endpoints	Hypothesis^**a**^

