**Primary**		
To measure whether use of individualized preventive care recommendations is likely to help patients live a longer, healthier life	**Change in quality-adjusted life expectancy (QALE)** at 6 months, in patients whose providers are in the intervention arm, as compared with the control arm.^b^	Higher

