### Power

A sample size of 60 providers (30/arm), each with 10 patients, will have 86.2% power to detect a clinically meaningful 3.0-month difference in the change of QALE between the 2 arms. We assume a small intra-cluster correlation coefficient (ICC)=0.01 because life expectancies of different patients are unlikely to be correlated, even from the same provider. In sensitivity analysis, estimated power is 80.4% for a sample size of 54 providers and an ICC=0.02. Therefore, the study will still have adequate power if 10% of patients are lost to follow-up, consistent with our pilot study [20].

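### The analysis section names an equivalence design, while the hypothesis, the endpoint table, the power statement and the section's own reasoning all describe a superiority comparison

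*Protocol article*

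**What the plan says.** The inferential framework is named once, in the Statistical analysis section: "The biostatistician will conduct analyses based on an equivalence design, with a modified intention-to-treat (ITT) patient population". That section goes on to specify linear mixed-effect models with random intercepts for patient and provider. It adds that a full ITT analysis is not expected to reach significance, because about one third of primary care patients miss or cancel scheduled encounters.

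The other statements about the primary question are these:

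- Abstract, Methods: "We hypothesize that quality-adjusted life expectancy will increase by more in patients who receive the intervention, as compared with controls".
- Endpoints: "The primary objective is to measure whether use of the tool improves patient quality-adjusted life expectancy (QALE), at a 6-month timeframe".
- Table 3, primary row: change in QALE at 6 months "in patients whose providers are in the intervention arm, as compared with the control arm", with the hypothesis column reading Higher.
- Power: with 30 providers per arm and 10 patients per provider, the section claims that the trial "will have 86.2% power to detect a clinically meaningful 3.0-month difference in the change of QALE between the 2 arms". The ICC behind this figure is 0.01. As a sensitivity case the section reports that "estimated power is 80.4% for a sample size of 54 providers and an ICC=0.02".

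No equivalence margin appears anywhere in the article. The Power section gives no standard deviation, alpha or sidedness.

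**The concern.** An equivalence analysis has as its null hypothesis that the arms differ by at least a margin. Rejecting that null supports the claim that the arms are alike. A superiority analysis has as its null that the arms do not differ, and rejecting it supports the claim that the tool helps. The two frameworks have different nulls and different success criteria, and they read an estimate near zero in opposite ways.

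The article states a directional hypothesis and an effect to be detected, then names the framework designed to show that no material effect exists. What is at stake is the published rule by which the primary result will be judged. With the word left in place, a non-significant difference could be presented as a successful equivalence finding. A sound positive result could equally be challenged as a departure from the published plan.

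**Working it through.** **1. The statements side by side.**

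| Place in the article | What it implies |
|---|---|
| Statistical analysis, opening sentence | Equivalence |
| Abstract, Methods | Larger QALE gain with the tool: superiority |
| Endpoints, primary objective | Does the tool improve QALE: superiority |
| Table 3, primary row | Hypothesis Higher: superiority |
| Power | Detect a 3.0-month difference: superiority |
| Statistical analysis, remark on full ITT | Dilution prevents significance: superiority |

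The last row deserves a closer look. If about one third of the full ITT population never has the encounter and gains nothing, a 3.0-month effect shrinks to about 3.0 × 2/3 = 2.0 months. A smaller difference is harder to detect but easier to declare equivalent. The authors' reasoning therefore works only for a test of difference.

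**2. The stated power.** The 86.2% cannot be reproduced outright, because SD and alpha are not given. It can be inverted under an assumed alpha. From the Power section: 30 providers per arm, 10 patients each, ICC 0.01, difference 3.0 months.

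- Design effect = 1 + (10 − 1) × 0.01 = 1.09.
- Assuming two-sided 5%: SE = 3.0 / (1.960 + 1.089) = 0.984 months.
- SE = SD × √(2 × 1.09 / 300), so SD = 0.984 / 0.0852 ≈ 11.54 months.
- Assuming one-sided 5% instead, the implied SD is 12.87 months.

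**3. Consistency with the second power figure.** For 54 providers (27 per arm) and ICC 0.02, the design effect is 1.18. With SD 11.54, SE = 11.54 × √(2 × 1.18 / 270) = 1.079 and 3.0 / 1.079 = 2.780. The power is then Φ(2.780 − 1.960) = 79.4%.

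| SD back-solved from 86.2% under | Power in the second case (stated: 80.4%) |
|---|---|
| Superiority, two-sided 5% | 79.4% |
| Superiority, one-sided 5% | 80.2% |
| Equivalence, margin 3.0, true difference 0, one-sided 5% tests | 77.3% |
| Equivalence, margin 3.0, true difference 0, one-sided 2.5% tests | 76.2% |

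The two stated figures fit each other somewhat better under superiority, but the separation is only a few points. This supports the reading and does not prove it.

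**4. What a literal equivalence test would do (illustration).** Assume a margin of 3.0 months, the only difference the article gives, with SE 0.984 and two one-sided 5% tests. For true difference d, the probability of success is Φ((3.0 − d)/SE − 1.645) − Φ((−3.0 − d)/SE + 1.645).

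- d = 0: 3.0/0.984 = 3.049, so 2Φ(3.049 − 1.645) − 1 = 2Φ(1.404) − 1 ≈ 84%.
- d = 3.0: Φ(−1.645) minus a negligible term ≈ 5%.

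With one-sided 2.5% tests the results are about 72% and 2.5%. The second result of each pair is true by construction, because a test evaluated at its own margin succeeds at about its alpha.

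**The case against.** The strongest reply is that this is a mislabel and nothing more. The objective, hypothesis, endpoint table and power text all point one way. The mixed model is the same under either framework, and the remark on full ITT shows that the authors were thinking of a test of difference. Without a margin, nobody could run an equivalence test from this text. Much of this stands. A reader might infer that the trial is set to answer the opposite question and that a real benefit will be scored as failure. The article does not support that, since it never specifies a workable equivalence test and its other statements contradict one.

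Three further inferences also go too far:

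- That the 86.2% demonstrably belongs to a superiority test. The wording about detecting a difference is good evidence, but without SD, alpha or sidedness the figure itself cannot settle the matter.
- That a two-sided 5% test matches the power paragraph. Sidedness is not stated, and the one-sided version fits the second power figure slightly better.
- That the SAP and full protocol carry the same word. Neither is shown.

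The reply does not remove the point. The article makes an affirmative statement about its primary inferential framework, and that statement is wrong against the rest of the text. It is not a detail that an article would normally leave to another document.

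**Conclusion.** The contradiction holds on the text alone and needs no computed figure. The article misnames the framework of its primary analysis, and with it the null hypothesis and the criterion for success. It is probably a slip of wording. The practical harm is an ambiguous rule that leaves room to read a null result as success, not a demonstrated reversal of the trial's conclusion. It should be corrected before outcomes are analysed, because the framework fixes what the trial may conclude.

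The 84% and 5% figures show the direction of the problem only. They rest on an assumed 3.0-month margin, an assumed two-sided 5% level behind the stated power, one-sided 5% equivalence tests and an SD back-solved from these. They should carry no weight as properties of this trial.

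**What to change.** In the Statistical analysis section, replace the reference to an equivalence design with a superiority design. State that the primary test is of no difference between arms in mean 6-month change in QALE, reported with its confidence interval. Give the alpha and sidedness that the sponsor actually used to obtain 86.2%. Two-sided 5% is the conventional choice, but the sponsor must confirm it because the article does not say. Check whether the full protocol and the SAP use the same word, and correct them if they do.

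The cost is a sentence or two of text, with whatever approvals the article's Oversight section requires for an amendment if the full protocol also has to change. Sample size, stated power, endpoint and model stay as they are.

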**Secondary**		
To measure whether use of individualized preventive care recommendations is likely to help patients live a longer, healthier life	**Change in QALE** at each of the following time points: 12 months, all follow-up time points.	Higher
To measure whether use of individualized preventive care recommendations is likely to help patients live a longer life	**Change in life expectancy** (not quality-adjusted) at each of the following time points: 6 months, 12 months, all follow-up time points.	Higher
To assess comprehension of the decision tool	**Comprehension** of preventive services most likely to impact a patient’s quality-adjusted life expectancy, assessed by correct identification of each of the following: a. Service most likely to improve his/her QALE b. Service least likely to improve his/her QALE c. Correct identification of a patient’s true age (the age most commonly associated with his/her quality-adjusted life expectancy), in relation to his/her biological age	Higher
To assess readiness to change	Share of preventive services ready to change over the next 1 month, assessed by percent of patients with a mean score ≥6 on a 7-point scale for the (a) top-ranked and (b) bottom-ranked individualized preventive care recommendations.^b^	Higher
To assess use of use of shared decision-making	Use of shared decision-making (SDM), assessed by score on SDM-Q-9 survey [25, 26]	Higher
To assess utilization of specific services^c^	Change in weight, systolic BP, HbA1c, 10-year ASCVD risk score, LDL, total cholesterol, dietary quality (Starting the Conversation assessment) [27, 28], physical activity (modified International Physical Activity Questionnaire-Short Form) [29, 30], alcohol misuse (AUDIT-C) [31, 32], tobacco cessation; receipt of screening for cancers of the breast, cervix, colorectum, lung.	Improved (higher or lower depending on service)

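### The stated patient and provider random intercepts protect the 6-month comparison only for some choices of response, and the article does not say which: if QALE levels are modelled, provider clustering of the change drops out of the standard error

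*Protocol article*

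**What the plan says.** All places are in the protocol article.

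- **Endpoint.** Collection of study endpoints defines the primary outcome as "change in patient QALE between the baseline encounter and 6 months later", which is one value per patient. Table 3 agrees.
- **Later time points.** Table 3 lists change in QALE as a secondary endpoint "at each of the following time points: 12 months, all follow-up time points". The data would allow this: "Inputs will be obtained from an EHR data feed for each patient, from the baseline encounter through study completion".
- **Model.** Statistical analysis states: "Linear mixed-effect models with random intercepts at the patient and provider levels will be used". It names no response, time term or fixed effect. It adds only that such models assume data missing at random.
- **Allocation.** The provider is the unit of randomization: "Provider randomization will be stratified by site (1:1 allocation ratio) in permuted block sizes of 2, 4, and 6".
- **Power.** The section states: "A sample size of 60 providers (30/arm), each with 10 patients, will have 86.2% power to detect a clinically meaningful 3.0-month difference". What is compared between arms is the QALE change, and the assumed ICC is 0.01. A sensitivity case with 54 providers and an ICC of 0.02 gives 80.4%.

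**The concern.** Treatment is assigned to providers and delivered by them, so the standard error of the arm comparison must carry provider-to-provider variation in the quantity compared. That quantity is the change in QALE. A provider random intercept does this when the response is a change. When the response is the QALE level at each visit, the same intercept describes how providers' patients differ in level and says nothing about how they differ in change.

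The model sentence leaves the choice open. The usual reason for a patient intercept is repeated measurement of a level, so the levels version is a live possibility. The Power section blurs the same line: it powers on change but justifies the small ICC by saying that patients' life expectancies are unlikely to be correlated, which is an argument about levels. Providers trained to use a tool can differ in the change they bring about even if their patients' life expectancies are uncorrelated.

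At stake is the validity of the primary standard error: confidence intervals that are too narrow and a false-positive rate above the nominal one.

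**Working it through.** **Inputs.** From Power: 60 providers (30 per arm), m = 10 patients each, so 300 patients per arm; ICC 0.01 and 0.02; difference 3.0 months; power 86.2% and 80.4%. The SD of the change, alpha and sidedness are not given. I assume a two-sided 5% test of a difference. An ICC of 0.05 is my own assumption, shown only for range.

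**The plan's own figure.** Without an SD, 86.2% cannot be reproduced directly, but it can be inverted.
- Design effect = 1 + (m − 1) × ICC = 1 + 9 × 0.01 = 1.09.
- Implied SE = 3.0 / (1.960 + 1.089) = 0.984 months.
- Implied SD = 0.984 / √(2 × 1.09 / 300) = 11.54 months.
- Check on the second figure: SE = 11.54 × √(2 × 1.18 / 270) = 1.079, and power = Φ(3.0/1.079 − 1.960) = 79.4%, against a stated 80.4%. A one-sided 5% test implies an SD of 12.87 and gives 80.2%.

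The two stated powers therefore agree within about one point with a clustered comparison of changes. The power calculation does count provider clustering of the change.

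**Three readings of the model sentence.** Let i be the patient and j the provider.

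*A. One 6-month change per patient.* D_ij = arm + provider_j + patient_ij + error_ij. With one value per patient, patient_ij and error_ij cannot be separated. The patient term is redundant. The provider term and the arm contrast remain estimable.

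*B. Baseline and 6-month levels with arm-by-time.* Y_ijt = fixed effects + provider_j + patient_ij + error_ijt. Subtracting, Y_ij1 − Y_ij0 = fixed effects + error_ij1 − error_ij0. Both intercepts vanish. The model SE is SD × √(2/300), while the true SE is SD × √(2 × (1 + 9 × ICC)/300). Hence type I error = 2 × [1 − Φ(1.96 / √(1 + 9 × ICC))].

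| ICC of change | Design effect | 1.96/√(design effect) | Type I error (formula) | Type I error (simulated, 20,000 runs) |
|---|---|---|---|---|
| 0.01 (stated) | 1.09 | 1.877 | about 6.0% | 6.3% |
| 0.02 (stated) | 1.18 | 1.804 | 7.1% | 7.0% |
| 0.05 (assumed) | 1.45 | 1.628 | 10.4% | 10.1% |

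The simulated column tests the changes with providers ignored, which is what B amounts to in balanced data. With 9 patients per provider after 10% loss, the formula gives 5.9% and 6.9% at the two stated ICCs. Fitted mixed models show the same mechanism. In SD units the mean model SE was 0.081 at ICC 0.01 and at 0.05, against true values of 0.085 and 0.098. Those fits used 60 data sets per ICC, enough for the SE but too few for a rejection rate.

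*C. Change values at 6 and 12 months or more.* Each patient now has several changes, so both intercepts are identifiable and the provider intercept carries clustering of the change. Fitted SEs were 0.087 and 0.097 in SD units at ICC 0.01 and 0.05, close to the true 0.085 and 0.098. A provider-level t test, used as a stand-in, had type I error of 4.9% to 5.4%. The fits took a provider's effect on the change to be the same at both visits.

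**The case against.** The strongest reply is that reading C fits both the model sentence and the data plan. Table 3 lists later time points, the data feed runs to study completion, the article speaks of models in the plural, and power is stated for a difference in change. This stands: a reader who infers that the stated model cannot fit the primary endpoint goes further than the document allows. But the article does not state C, and Table 3 makes the later time points secondary. Patient surveys are taken only at baseline and 6 months, and they may supply the diet, activity, alcohol and tobacco inputs. A primary analysis that depends on pooling later visits should say so.

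Reading A does little harm, as the reply would also point out. Only a surplus term is involved.

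A reader might also infer that the analysis omits the site strata and baseline QALE. The document does not support that. The sentence names random effects only and lists no fixed effects at all, not even arm. Covariates are commonly left to a full protocol or SAP, neither of which is shown here. Any precision gain from adjustment would depend on a correlation between baseline and change that the article does not give.

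Finally, the inflation at the trial's own ICCs is modest. That is correct, and the 10% figure should not be quoted without its assumption.

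**Conclusion.** The point holds in a limited form. The sentence that governs the primary test admits one reading with a redundant term, one that is anti-conservative and one that is adequate. Under the anti-conservative reading, the SE is too small by a factor of √1.09 = 1.044 at ICC 0.01 and √1.18 = 1.086 at ICC 0.02. A nominal 5% test then runs at about 6.0% and 7.1%. These figures assume a two-sided test of a difference, 10 patients per provider, and that the stated ICCs describe the change. They do not depend on the unstated SD.

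This is more than missing detail, because the random effects are stated and in one natural use they leave out the clustering that the power calculation counts. It does not show that the trial's analysis will be invalid. The change should be made, and settled before outcomes by arm are seen, since the Blinding section exempts the study biostatistician from blinding.

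**What to change.** Make the primary model the 6-month change in QALE on arm, with a provider random intercept only and Kenward-Roger or Satterthwaite degrees of freedom. Where QALE levels are modelled longitudinally, including the all-time-points analysis, add a provider-by-time random effect alongside the patient effect. If repeated change values are what is intended, say so and define the 6-month contrast that is the primary test.

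Adjustment for baseline QALE and site is an optional precision gain of unknown size.

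The cost is a few lines of wording and code. Compared with a levels model using intercepts alone, intervals widen by about 4% at ICC 0.01 and 9% at ICC 0.02, plus a little for the small-sample degrees of freedom. Apart from that small-sample allowance, no planned power is lost, because the stated 86.2% already allows for clustering at ICC 0.01. With the back-solved SD of 11.54 months, power at 60 providers and ICC 0.02 is 83.4%.
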